**Figure 1 figure1:**
[figure not shown]
Flow chart of the study.

### Instrument

ActiGraph WGT3X-BT accelerometers were chosen to measure MVPA and sedentary time behavior. ActiGraph sensors have been widely studied and have shown adequate reproducibility, validity, and feasibility for children and adolescents [21].

Participants will wear the ActiGraph WGT3X-BT accelerometer for 7 full, consecutive days, including weekdays and weekends. It will be worn on the wrist of the nondominant hand. This technique is the most reliable method to record and store the amount of PA quantitatively, allowing us to determine and compare levels of PA demonstrated by each individual in a given period [4,15]. In addition, like other authors, diary recordings will be collected with data such as sleep time, mode of transportation to school or other places, and the kind of PA they engage in [22-24].

To conduct this protocol, 50 ActiGraph WGT3X-BT accelerometers were purchased along with the ActiLife 6 ActiGraph PA software. All the accessories necessary for its use were also purchased, including Velcro wrist straps and cables for data transfer. The accelerometer will be worn on the nondominant wrist for 7 full, consecutive days (worn on day 1 and removed on day 8) including weekdays and weekends. The accelerometer consists of a triaxial activity monitor to capture and record continuous, high-resolution PA and sleep and wake information that provides the following measurements: acceleration, energy expenditure, steps, PA intensity, body position, and lighting ambient.

### Data Collection

Each participant will be identified by a unique and confidential numerical code, which is assigned after informed consent is obtained from the legal guardians. Those responsible for the database must save the files on servers with a password. To determine the codes, the following process is followed:

Province: 1=Araba, 2=Bizkaia, and 3=Gipuzkoa.Town (000)—each town is assigned a 3-digit number (eg, 001, 002, etc)Education center is assigned a 3-digit number (eg, 001, 002, etc).The academic stage between primary, secondary, or high school or secondary vocational training (1, 2, and 3)The gradeThe classroom in letters A, B, C, and DThe student number (00) considering that each classroom will have a maximum of 30 students.

Consequently, each participant will have a 12-digit code; for example, 2 022 060 11 D 07.

Prior to data collection, the study presentation brochure was emailed to the centers inviting them to participate, along with the informed consent document to authorize their children to participate in the study. Each center shares information about the study with the families through the established communication channel in each case (web platform or email), sending the legal guardians the information received at the center.

If families are interested in participating, they must send their informed consent to the head of the education center, and depending on the number of volunteers, a random draw will be held until the sample requirements established in each area and center are reached.

### Programming and Downloading Accelerometry Data

The computer operating system, compatible with ActiGraph software, has the software license to download the data. Before starting data logging with the accelerometer, each device will be turned on or programmed for data logging.

To program the accelerometer, the participant’s date of birth, gender, height (cm), body mass (kg), and dominant hand must first be recorded. These data will be requested after receiving informed consent. It will be important to inform the participant how to wear the accelerometer before putting it on. The accelerometer can be placed either in contact with the skin or over a sleeve in case of allergies by touch with the parts of the device [25].

The accelerometer is placed on the nondominant wrist without being too tight so that it is not uncomfortable, nor so loose that it moves around the wrist. The part of the button to close the band should be facing toward the fingers of the hand (as if it were a watch). In addition, instructions with photographs will be sent to explain the placement of the accelerometers. The accelerometer should be worn all day and night and should only be removed during activities where the accelerometer could be submerged in water (bathing, showering, water activities, etc). In these situations, it must be removed and put back on the same wrist after the activity is finished.

During the week that the accelerometer is worn, participants must complete a diary to record their hours of daily activity: the time they wake up, nap, sleep, mode, and duration of travel to class, mode and duration of travel to other places, physical education class, scheduled and unscheduled PA, the time when the accelerometer was removed, and circumstances that may have affected their sleep/wake pattern (travel, illness, etc).

With the youngest children, it is important to understand that the diary will often be completed by the parents, guardians or even their teachers. Similarly, from the age of 8 years, children should be encouraged to help their parents or guardians to complete the diary. However, adolescents will be encouraged to complete their diaries themselves, as their parents are often unaware of their sleep routines [25].

Once the full 7 days have elapsed, on the agreed upon date, the accelerometer will be delivered to the person in charge (the teacher or researcher) along with the daily activity log sheet, only including the participant´s code.

Once the accelerometer and the daily activity record sheet have been collected, the data will be downloaded [26]. As this study is conducted with children, the originals will be converted to 60 seconds to calculate sleep [27] and to 5 seconds for daily PA [27,28].

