### Study Variables

The following study variables will be recorded: (1) active time and sedentary behavior (in the overall school schedule, physical education classes, school recess time, activities related to school sports and other organized and unorganized exercise, the rest of the time during the day while awake, school days, nonschool days, bouts of light PA, moderate PA, vigorous PA, and MVPA); (2) time asleep (school days, nonschool days, and bouts of sleeping time); (3) type of transportation to school (bus, car, motorcycle, or any other means that do not involve active travel, and time or day of using transportation); (4) type of transportation to places other than school (bus, car, motorcycle, or any other means that do not involve active travel, walking, cycling, or skating); and (5) grade students are attending, BMI, type of centers, location, and socioeconomic status.

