### Statistical Analysis

The statistical analysis will be performed using SPSS (version 27.0.1.0; IBM Corp). Parametric tests will be performed after all assumptions for each test are met. For comparison between groups (girls vs boys, age groups, school types, and regions) 2-tailed *t* tests, 1-way analysis of variance, or the nonparametric method of Kruskal-Wallis and chi-square tests will be used for the main primary outcomes as dependent variables.

Descriptive statistics will be used for all outcome variables, and the effect size and the level of significance corresponding to the main group (between participants) will be reported. To prevent a type I error, post hoc comparison will be performed when a significant interaction effect is present. Values will be expressed as mean (SD). The significance level will be set at 95% (α=.05).

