## Discussion

### Expected Findings

This study aims to provide current estimates of the levels of PA, sedentary behavior, and sleep among children and adolescents in the BAC (6-17 years old). Sedentary behavior is fundamentally important in the health of children and adolescents [29], and it is highly influenced by the social environment in which they live [30]. Recent statistics show that 28% of children in Spain between the ages of 3 and 8 years are overweight, and 9% are obese [31]. It is clear that increased PA and reducing sedentary behavior play a leading role in preventing overweight and excess adiposity, even when people present an adverse genetic condition that predisposes them to be obese [32]. Some studies seem to have shown an inverse relationship between MVPA with adiposity and cardiometabolic risk, and a positive relationship between MVPA with cardiorespiratory fitness and total body bone mineral density among children and adolescents [33]. Other studies maintain that screen time has a significant and inverse relationship with hours of sleep, unregulated activity (games and other activities), and physical exercise [34].

The results of this study intend to demonstrate significant differences in PA levels in different age groups since the volume of school PA in the BAC decreases as the age of the schoolchildren increases. In terms of gender, it is higher among boys than in girls, reaching the same conclusions as other authors [35,36].

The results will be used to analyze and assess the relevance of creating a battery of assessment of physical condition in the Basque Government (interdepartmental) as an improvement in the diagnosis of the state of physical condition and to be able to intervene from the department of education and the department of health to address, together with the Directorate of Physical Activity and Sport the concrete actions to be developed as process improvement and move in an improvement of physical conditions in future evaluations.

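### The usual diary reporter shifts with the child's age and is not among the recorded items, so age differences in diary-based variables (transport, activity context) would mix behaviour with a change of reporter; minor

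*Protocol article*

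**What the plan says.** The diary procedure is in the protocol article under Programming and Downloading Accelerometry Data. For the youngest children, "the diary will often be completed by the parents, guardians or even their teachers". Next, "from the age of 8 years, children should be encouraged to help their parents or guardians to complete the diary". Finally, "adolescents will be encouraged to complete their diaries themselves, as their parents are often unaware of their sleep routines".

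Under Instrument, the article says that "diary recordings will be collected with data such as sleep time, mode of transportation to school or other places, and the kind of PA" will be obtained this way. The diary content listed under Programming and Downloading Accelerometry Data adds wake and nap times, travel duration, physical education, scheduled and unscheduled activity, and device removal.

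Study Variables includes active and sedentary time during "activities related to school sports and other organized and unorganized exercise", and "type of transportation to school (bus, car, motorcycle, or any other means that do not involve active travel", with a matching item for travel to other places.

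The group comparisons are introduced under Statistical Analysis with "For comparison between groups (girls vs boys, age groups, school types, and regions", and are for the main primary outcomes. Expected Findings states that "The results of this study intend to demonstrate significant differences in PA levels in different age groups". Future Prospects names mobility and activity levels at different ages as a later use of the data.

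**The concern.** The person supplying the diary information tends to change along the same axis, age, on which groups are compared. The protocol's own reason for adolescent self-report is that parents often do not know adolescents' sleep habits, so it accepts that reporters differ in what they know. Teachers may also fill in diaries for the youngest, and no limit is stated on which items they enter. Several listed items, such as evening travel or weekend activity, lie outside what a teacher normally sees.

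If diary variables are then compared by age, a difference could reflect how a parent, a teacher or a teenager reports rather than what children do. This bias does not shrink as the sample grows. If nobody notes who completed the diary at the time, it cannot be recovered at analysis.

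**Working it through.** **1. Which variables depend on the diary.**

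| Variable | Described source | Exposed to a change of reporter? |
|---|---|---|
| Activity intensities, sedentary time, total bedtime, total sleep time, sleep efficiency | Raw accelerometer data (Abstract, Methods) | Not unless diary times enter the scoring; the article does not say they do |
| Transport type and duration, to school and elsewhere | Diary only (Instrument; Programming and Downloading Accelerometry Data) | Yes |
| Active time in organized and unorganized exercise outside school | Amount from the accelerometer, context label from the diary | Yes, through the label |

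**2. Whether the reporter is recorded.** It appears neither in the diary items under Programming and Downloading Accelerometry Data nor among the five groups of items under Study Variables.

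**3. Form of the bias.** Simplify to two reporter types. Let δ be the mean difference in what self-report and proxy report record for the same behaviour, and let p be the share of self-reported diaries. With no true age difference, the older-minus-younger contrast is δ × (p_old − p_young). The article gives none of these three quantities. Only p could be learned from a reporter field, and δ could then be judged from children of similar age with different reporters.

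**4. Group sizes.** The concern rests on no stated figure, but the group sizes come from the sample plan, which reproduces: 2² × 0.25 / 0.03² = 1111.1, against the stated 1111. From the total columns of Table 1:
- primary: male 44+44+48+48+49+49 = 282, female 43+42+44+47+47+45 = 268, together 550;
- secondary and high school: male 50+48+48+47+48+48 = 289, female 47+46+45+45+45+44 = 272, together 561;
- sum 550 + 561 = 1111. The first two primary grades alone give 44+43+44+42 = 173.

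These school stages only approximate the reporter groups. The article fixes no age for *youngest* or for adolescence.

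**5. Yardstick, on assumed shifts.** In SD units, SE = √(1/n₁ + 1/n₂). For 550 against 561 this is 0.060; for 173 against 561 it is 0.087. The chance that a net reporter shift d, with no true age difference, is declared significant at two-sided 0.05 is Φ(d/SE − 1.96) + Φ(−d/SE − 1.96):

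| Assumed net shift d (SD) | 550 vs 561 | 173 vs 561 |
|---|---|---|
| 0.05 | 0.133 | 0.089 |
| 0.10 | 0.385 | 0.210 |
| 0.15 | 0.705 | 0.407 |
| 0.20 | 0.915 | 0.633 |
| 0.30 | 0.999 | 0.932 |

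For a yes/no variable such as active travel, with an assumed proportion of 50% (SD 0.5), the shift that just reaches significance is 1.96 × 0.5 × 0.060 = 0.059, or 5.9 percentage points, for 550 against 561. For 173 against 561 it is 1.96 × 0.5 × 0.087 = 0.085, or 8.5 points.

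All of this assumes simple random sampling. Clustering by school would raise the SE and lower these probabilities, but would leave the bias unchanged. The table shows how small a shift the sample could pick up; it does not show that such a shift exists.

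**The case against.** The strongest reply is that the age comparisons actually named are for the main primary outcomes. The main objective is activity, sedentary behaviour and sleep, and these are scored from one device at every age. This stands. A reader might infer that the age differences in activity levels which the study intends to show, or its sleep results, are confounded by reporter. The documents do not support that: those measures do not rest on diary reports as described, and no age comparison of diary sleep times is announced. An age comparison of transport or activity context is likely, given Study Variables and Future Prospects, but it is not spelled out.

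A second reply is that the age pattern is guidance. The text says *often* and *encouraged* and sets no fixed rule, so a reader who sorts the sample into strict proxy, mixed and self-report groups goes beyond it. This also stands. It cuts both ways: the confounding is weaker than a strict rule would produce, and some overlap between reporters is likely.

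Third, adapting the reporter to age is reasoned and referenced, and one reporter type from 6 to 17 years is hardly feasible. That is fair; the point does not ask for it. Nor does the text say that teachers enter bedtimes or out-of-school items; it only leaves this open.

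Fourth, the diary form is not shown, and the full form may carry a box for the person completing it. That possibility remains. What can be said is that the article's lists of diary items and study variables do not include it. If the form does, the first part of the fix is already met. A by-reporter analysis may also sit in an analysis plan, but it could not be carried out without the field.

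**Conclusion.** The point holds for diary-only variables (transport type and duration) and for active time split by diary-defined context. For these, an age difference could not be attributed to behaviour alone unless the reporter is known. It does not reach the accelerometer-scored activity, sedentary and sleep outcomes, provided that diary bedtimes and removal times do not enter their scoring; the article does not say that they do.

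The size is unknown. The article gives no SD, no reporter effect and no reporter mix, so the probabilities and percentage-point thresholds shown are illustrations under stated assumptions. The conclusion assumes that the article's item lists reflect the actual form. Severity is minor: it is a cheap improvement to secondary descriptive variables and does not threaten the main objective.

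**What to change.** For participants still to be measured:

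1. Add a tick box to each diary day: completed by child / child with parent / parent or guardian / teacher.
2. In the family and school instructions, ask that a parent or guardian, rather than a teacher, enter out-of-school items for younger children.
3. For diary-based variables, show age comparisons by reporter where reporter types overlap. Where they do not, state that age and reporter cannot be separated, and do not present the contrast as an age effect.

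No change is needed to the accelerometer scoring of sleep and activity on this account.

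The cost is one box, one line of instructions and one additional tabulation. There are two downsides. The field is missing for the 341 already measured, which leaves 1111 − 341 = 770 (770/1111 = 69%) who could carry it; on the Abstract's statement of up to 50% recruited, it would be about half. And overlap between the youngest and oldest children will be small, so the by-reporter comparison will be most informative in the middle ages.

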### Study Variables

The following study variables will be recorded: (1) active time and sedentary behavior (in the overall school schedule, physical education classes, school recess time, activities related to school sports and other organized and unorganized exercise, the rest of the time during the day while awake, school days, nonschool days, bouts of light PA, moderate PA, vigorous PA, and MVPA); (2) time asleep (school days, nonschool days, and bouts of sleeping time); (3) type of transportation to school (bus, car, motorcycle, or any other means that do not involve active travel, and time or day of using transportation); (4) type of transportation to places other than school (bus, car, motorcycle, or any other means that do not involve active travel, walking, cycling, or skating); and (5) grade students are attending, BMI, type of centers, location, and socioeconomic status.

### Ethical Considerations

This study was approved by the Euskadi Drug Research Ethics Committee (Basque Government Department of Health) in accordance with law 14/2007 on biomedical research, ethical principles of the Declaration of Helsinki, and other ethical principles and applicable legislation with internal code PI2020011. In turn, current regulations on the protection of personal data will be followed: Regulation (EU) 2016/679 of April 27, 2016 (GDPR), Organic Law 3/2018, of December 5 on Personal Data Protection and guaranteeing digital rights (ES), and Royal Decree (ES) 1720/2007 of December 21.

### Statistical Analysis

The statistical analysis will be performed using SPSS (version 27.0.1.0; IBM Corp). Parametric tests will be performed after all assumptions for each test are met. For comparison between groups (girls vs boys, age groups, school types, and regions) 2-tailed *t* tests, 1-way analysis of variance, or the nonparametric method of Kruskal-Wallis and chi-square tests will be used for the main primary outcomes as dependent variables.

Descriptive statistics will be used for all outcome variables, and the effect size and the level of significance corresponding to the main group (between participants) will be reported. To prevent a type I error, post hoc comparison will be performed when a significant interaction effect is present. Values will be expressed as mean (SD). The significance level will be set at 95% (α=.05).

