Interventions promoting PA among children and adolescents must be supported by evidence that provides us the necessary information to do so efficiently. This study will allow us to analyze different realities (at different times, school settings, and ages), ultimately facilitating the design of policies and programs to promote PA and health on the basis of stated evidence [15]. Moreover, in the Basque Autonomous Community (BAC), there is a lack of evidence regarding the level of PA among children [16].

To determine the level of PA in the school population aged between 6 and 17 years in the BAC, and considering the benefits of PA for children and adolescents [17,18], this protocol aims to determine whether this group meets the established parameters of daily PA recommended by the WHO [2]. We hypothesize that >50% of the children do not meet the WHO recommendations, and that the level of PA in boys is greater than that in girls.

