### Participants and Selection Criteria

According to data extracted from the Basque Statistics Institute (EUSTAT) [19], as of October 16, 2020, the reference population to extract the sample residents in the BAC, aged between 6 and 17 years (born between 2003 and 2014), is 254,093 people, of whom 130,645 are boys and 123,448 are girls.

The corresponding sample size, considering that we are referencing a universal population greater than 100,000 people (referred as infinite for sample size calculation) is 1111 participants, at a confidence level of 2σ of 95.5%, an error limit of 3%, and heterogeneity of 50% [20]. To ensure a proportionate distribution of the sample in all age groups, territories, public and private centers, as well as girls and boys, these 1111 people were selected in accordance with the distribution detailed in Table 1. This sample is defined for all the assessment tests that comprise the project.

There is a proportional and random stratification based on province and county, age, gender, education network (public or private), and medea (socioeconomic level based on the deprivation index per census section, which enables the identification of sections with socioeconomic conditions), along with some inclusion and exclusion criteria that are listed in Textbox 1. Schools were selected randomly on the basis of the above-mentioned criteria.

**Table 1 table1:** Sample size and the current sample (N=1111).

Grade	Araba province				Bizkaia province				Gipuzkoa province				Total			
	Male		Female		Male		Female		Male		Female		Male		Female	
	Sample, n	Current sample, n	Sample, n	Current sample, n	Sample, n	Current sample, n	Sample, n	Current sample, n	Sample, n	Current sample, n	Sample, n	Current sample, n	Sample, n	Current sample, n	Sample, n	Current sample, n
First primary	8	9	7	8	22	6	21	6	14	1	14	1	44	16	43	15
Second primary	7	8	7	8	22	5	21	5	15	1	14	1	44	14	42	14
Third primary	8	8	7	7	23	5	22	5	16	1	15	1	48	14	44	13
Fourth primary	8	8	8	8	24	6	23	6	16	1	16	1	48	15	47	15
Fifth primary	8	6	8	7	24	6	23	6	17	0	16	1	49	12	47	14
Sixth primary	8	6	7	6	24	6	23	8	17	1	16	0	49	13	45	14
First secondary	8	7	7	6	25	4	24	5	17	0	16	1	50	11	47	12
Second secondary	7	6	7	6	25	4	22	5	17	1	16	0	48	11	46	11
Third secondary	7	8	7	7	24	4	22	10	17	0	16	1	48	12	45	18
Fourth secondary	7	8	7	8	24	10	23	8	17	1	16	0	47	19	45	16
First high school	7	8	7	7	24	8	23	14	16	1	16	1	48	17	45	22
Second high school	7	8	7	7	24	3	22	3	17	1	15	1	48	12	44	11

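### The named group tests take one factor at a time despite a sample stratified on five, so the boys-girls contrast on continuous outcomes is valid but may be less precise than the design allows

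*Protocol article*

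**What the plan says.** Participants and Selection Criteria (protocol article) describes "proportional and random stratification based on province and county, age, gender, education network (public or private), and medea", the last being a census-section deprivation index. Table 1 sets quotas by 12 grades, sex and three provinces, totalling 571 boys and 540 girls.

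The Background states two hypotheses: that more than half of the children miss the WHO recommendation, and that "the level of PA in boys is greater than that in girls". The abstract's Results and the Expected Findings section both anticipate differences in activity between age groups.

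Statistical Analysis opens its list of comparisons with "For comparison between groups (girls vs boys, age groups, school types, and regions) 2-tailed", which introduces the t test. The other methods it names are a 1-way analysis of variance, the Kruskal-Wallis test and the chi-square test, all applied to the primary outcomes. No factorial, adjusted or stratified model is named. The next paragraph nevertheless says that "post hoc comparison will be performed when a significant interaction effect is present". Study Variables lists grade, type of centre, location and socioeconomic status among the data recorded.

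**The concern.** Age is both a stratification factor and a factor the authors expect to matter. If boys and girls aged 6 to 17 are compared with an ordinary two-sample t test, the spread of activity across grades counts as random error. Since sex is planned to be balanced across grades, that spread could be removed without changing what is estimated. One of the two stated hypotheses would then be tested with a wider interval than the data could give.

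The section also does not fit together. A t test, a 1-way analysis of variance, a Kruskal-Wallis test and a chi-square test each examine one factor, so none produces the interaction on which the post hoc rule depends. Either a multi-factor model is intended and unnamed, or the rule can never be triggered. Deprivation is a stratifier but appears in none of the listed comparisons.

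**Working it through.** **1. The plan's own sample size.** The article gives "1111 participants, at a confidence level of 2σ of 95.5%, an error limit of 3%, and heterogeneity of 50" percent. With n = z²p(1−p)/e², z = 2, p = 0.5 and e = 0.03:

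n = 4 × 0.25 / 0.0009 = 1111.1, which reproduces 1111.

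This is a precision calculation for one proportion. The article states no power for the boys-girls contrast.

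**2. Is sex balanced over grade?** From the planned totals in Table 1:
- Boys by grade: 44, 44, 48, 48, 49, 49, 50, 48, 48, 47, 48, 48 (sum 571).
- Girls by grade: 43, 42, 44, 47, 47, 45, 47, 46, 45, 45, 45, 44 (sum 540).

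Chi-square is 0.14 on 11 df (p about 1.00), and the R² of sex on grade is 0.0001. Leaving grade out therefore costs precision and causes essentially no bias, provided the quotas fill.

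**3. Standard error of the unadjusted contrast**, in units of the outcome SD:

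SE = √(1/571 + 1/540) = 0.0600.

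The difference detectable with 80% power, two-sided α = 0.05, is (1.960 + 0.842) × 0.0600 = 0.168 SD.

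**4. Effect of adjustment.** If the strata explain a share R² of the outcome variance and are unrelated to sex, the SE is multiplied by √(1−R²). The equivalent extra sample is 1111 × [1/(1−R²) − 1]. R² is not in the article, so it is varied. The sex gap is not given either, so power is shown for three assumed gaps (normal approximation).

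| Assumed R² | SE ratio | Equivalent extra pupils | Power, gap 0.10 SD | Power, gap 0.15 SD | Power, gap 0.20 SD |
|---|---|---|---|---|---|
| 0 (as planned) | 1.000 | 0 | 38% | 70% | 91% |
| 0.02 | 0.990 | 23 | 39% | 71% | 92% |
| 0.05 | 0.975 | 58 | 40% | 73% | 93% |
| 0.10 | 0.949 | 123 | 42% | 75% | 94% |
| 0.20 | 0.894 | 278 | 46% | 80% | 96% |
| 0.30 | 0.837 | 476 | 51% | 85% | 98% |

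Eleven grade terms raise the SE by √(1109/1098) = 1.005, about 0.5%.

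**5. What an R² of that size would require.** Suppose only a straight-line age trend contributes. The variance of grade (coded 0 to 11) in the planned sample is 11.65, so a total fall of F SD from first to last grade gives R² = (F/11)² × 11.65:
- F = 0.5: 0.024
- F = 1.0: 0.096
- F = 1.75: 0.295

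The upper rows of the table therefore need a steep age gradient, or a sizeable contribution from the other strata.

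**6. Limits of the formula.** It applies to a continuous outcome and to the sex contrast, treating pupils as independent. It does not carry over to:
- the age comparison, where grade is the factor tested;
- network or region, which are contrasts between schools;
- the log odds ratio for meeting the recommendation.

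**The case against.** The strongest reply is that nothing here is invalid. An unadjusted comparison answers the stated hypothesis, the main objective is descriptive, and the sample size promises precision for one proportion rather than power for a sex contrast. All of that stands. The other hypothesis, on the share missing the recommendation, is a single proportion and is untouched.

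It can also be said that a condensed article may leave adjusted models to an analysis plan, and that the interaction sentence implies one exists. This stands in part: the absence of a covariate list would be no finding on its own. But the article does name the tests for its primary outcomes, and those tests conflict with its own interaction rule.

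A third reply is that the size of the loss is assumed throughout. That is correct. At a gap of 0.20 SD, power is already about 91% and adjustment adds little; at 0.30 SD it exceeds 99% without adjustment.

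Four stronger readings are tempting, and the article does not support them:
- **The t test is biased.** The planned counts by sex and grade are almost perfectly balanced. The 341 pupils recruited so far are less even in places (third secondary has 12 boys and 18 girls), but they are not the planned sample.
- **Every one-factor test loses precision in the same way.** Grade cannot be adjusted away when age is the comparison. For network and region, schools are selected first and pupils within them, so a pupil-level SE tends to be too small, not too large.
- **A logistic model would bring the same gain.** Covariate adjustment does not shrink the log-odds SE by √(1−R²). It generally increases it and changes the quantity estimated.
- **No multi-factor analysis is intended at all.** The interaction sentence points the other way.

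**Conclusion.** The point holds in a limited form. The article names only single-factor tests for a sample stratified on age, sex, province, network and deprivation, and its post hoc rule depends on an interaction that those tests cannot produce. For the boys-girls contrast on continuous outcomes, the planned test is valid but gives up whatever precision the strata could supply.

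The article does not allow that loss to be sized. It is negligible if the strata explain about 2% of the variance, modest at 5% to 10%, and material (SE about 16% smaller after adjustment) at 30%. At an assumed gap of 0.15 SD, power would rise from 70% to between 71% and 85% over that range. These figures assume that the quotas fill, that sex stays unrelated to the strata, and that clustering within schools is handled separately. This is a cheap improvement in efficiency and clarity, not the correction of an invalid analysis, and it does not affect the main descriptive aim.

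**What to change.** Amend Statistical Analysis as follows.

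- For each continuous primary outcome, estimate the boys-girls difference with a 95% CI from one linear model containing sex, grade, province, school network and medea category. Use standard errors that allow for pupils being sampled within schools.
- State that sex-by-age is the interaction to which the post hoc rule refers, so that the rule can operate.
- Keep crude group means (SD) as description.
- For meeting the WHO recommendation, if a model is used, report a marginal (standardised) risk difference with a 95% CI, and claim no precision gain from an adjusted odds ratio.
- Claim no precision gain for the age comparison or for network and region.

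The cost is revised wording, slightly more analysis work and a few degrees of freedom (about 0.5% of the SE for the grade terms). No new data are needed, because the adjustment variables are already recorded. Naming the model in advance also avoids choosing covariates after the data are seen.
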